### Measures

Anthropometric and sociodemographic data, information on clinical history, lung function, pulmonary exacerbations (number and time between exacerbations) and CF-associated admissions to hospital, number of days absent from work or school and CF-associated medical treatment and care are collected at pre-determined time points during the study period. Lung function measurement is performed at each study visit using the SpiroSense Pro^®^ spirometer (PARI GmbH, Germany), using the same technology as the home spirometer. Additionally, two different questionnaires, the German CF-questionnaire revised (CFQ-R) in its age-appropriate version and the EQ-5D-5L or EQ-5D-Y-5L in adolescents, respectively, are performed to assess the quality of life of all participants initially, during, and at the end of the study period (24–27). Participants will also be regularly screened for depressive disorders using the Beck Depression Inventar Fast Screen at each study visit (28, 29). Expectations regarding the new form of care applied in this study and their fulfilment are assessed at baseline and the end of the study period (see additional file “Questionnaire expectations conneCT CF”). Participants, their relatives, and CF physicians will be surveyed on acceptance, satisfaction, potential for optimization, barriers and implementation of this new form of care into standard care at the end of the study via a telephone interview (see Table 1).

### Endpoints

The primary endpoint is the time to first protocol-defined pulmonary exacerbation after initiation of the intervention phase. Secondary outcome measures include the number of pulmonary exacerbations, time between pulmonary exacerbations, adherence to inhalation therapy, changes of FEV1 and forced vital capacity (FVC) from baseline, the number of CF-associated hospital admissions, and changes in health-related quality of life (assessed with CFQ-R and EQ-5D-5L). Furthermore, sociodemographic and anthropometric data, number of days absent from work or school, and CF associated medical treatment and care are assessed by explorative analysis, and health care-related costs for both study groups are evaluated.

### Data management

At each study site, research personnel enter data from source documents into the electronic case report form (eCRF, EDC-Systems, secuTrial^®^). Data collected from the PARI Connect App can be accessed via a web-based dashboard. The data from the dashboard and all further data transfer within the study will be performed in pseudonymized form as comma-separated values (CSV) file via secure file transfer protocol (SFTP) server with exception of personal data needed for video-conferencing and telephone coaching. For video-conferencing, a secured web portal (m.Doc GmbH) is established with restricted access only for the participant and study personnel. All study collaborators will have equally access to the final trial dataset. Trial results will be published in peer-reviewed journals. Authorship eligibility is based on substantial contributions to the conception or design of the work; or the acquisition, analysis, or interpretation of data for the work.

### Quality assurance

Quality of medical data is ensured by intensive training of the participants in the use of the nebulizer, the app, and the performance on the home spirometry. Treatment plans entered into the app by the participants will be compared to those entered into the eCRF by the study personnel and checked at each study visit. To ensure safe data collection and data transfer, an extensive data protection concept compliant with GDPR (General Data Protection Regulation) has been elaborated. The study protocol has been designed according the standard ethical and scientific principles such as the declaration of Helsinki, guidelines of CIOMS (Council for International Organization of Medical Sciences) in collaboration with WHO (World Health Organization). Study sites report recruitment progress to all trial collaborators on a monthly basis. In case no data is tracked from the inhalation device or home spirometry, an alert to the study centres is created to ensure adherence to study measures. Study interventions are discontinued on patient’s request or in case of insufficient patient’s adherence to study interventions and study visits. Participant’s data will be collected and evaluated until discontinuation of study participation. An interim analysis will be performed after 12 months following study initiating. All study collaborators will have access to these interim results. Because of the minimal risk of the intervention, possible adverse events will be collected at routine study visits. For the same reason, a formal data monitoring committee is not needed.

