### Sample size calculation

Sample size calculation was performed by Private Institute for Applied Health Services Research (inav) GmbH and is based on the following assumptions: (1) primary endpoint: time to pulmonary exacerbation (30), (2) median time to exacerbation is 30% less in the CG compared to the IG based on estimation of involved CF experts, (3) event-free survival within 12 months in 25% of participants (18), (4) a significance level α = 0.05 and power of 1 – β = 0.8, (5) dropout rate of 20% (18) and (6) exponential distribution of survival and proportional hazards. Following these assumptions, a sample size of 391 participants is needed. To account for possible deviations from the assumed survival and dropout rate, we aim to recruit 402 patients. Participants are recruited as part of their routine visit at their CF centre by research personnel.

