Our study has some limitations: due to the study design’s nature, blinding of the patients and staff is not possible. Participation in this trial will be offered to all patients meeting the inclusion criteria. Nevertheless, only very motivated patients may agree to participate, leading to a selection bias. Additionally, a performance bias could occur because staff and patients of the participating centres might be more aware of the issue of adherence. This bias might lead to an increase in adherence also in the CG possibly diminishing our ability to detect differences in adherence between the IG and CG.

The coronavirus disease 2019 (COVID-19) pandemic has highlighted the importance and potential of digital technologies in patient care, and different strategies have been rapidly implemented (49–51). Scientific evidence for the feasibility, clinical benefit and cost-effectiveness of these interventions in patients with chronic conditions like CF is urgently needed to form the basis of a regulatory framework to authorize, integrate, and finance telemedicine services (52).

In summary, this study offers the opportunity to establish structures for secure data transmission, evaluate the use of telemedicine capable devices and adherence interventions on lung health and its cost-effectiveness, and possibly pave the way for implementation of telemedicine in routine care for patients with CF.

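### Interim results are open to every study collaborator of an unblinded trial whose primary event depends on a clinician's decision to give antibiotics

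*Protocol article*

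**What the plan says.** The protocol article places the interim analysis under Quality assurance. On timing and access: "An interim analysis will be performed after 12 months following study initiating. All study collaborators will have access to these interim results". On oversight, having argued that the intervention carries minimal risk: "For the same reason, a formal data monitoring committee is not needed". It gives no content, test or decision rule for the interim, does not define who the collaborators are, and states no limit on what they see.

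Three other places bear on this:

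- **Discussion (limitations):** "due to the study design’s nature, blinding of the patients and staff is not possible".
- **Study population and Endpoints:** the primary endpoint is time to first exacerbation after the intervention phase begins. An exacerbation requires that additional antibiotics were given, for at least two listed reasons, several of which are symptoms.
- **Statistical analysis plan:** all data are to be compared between the two arms. This is a general statement and does not mention the interim.

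**The concern.** In an unblinded trial the staff already know each patient's arm. They do not know how the arms compare overall. If comparative interim results reach them, they gain that knowledge while they are still deciding whether a patient with more cough or fatigue needs extra antibiotics. That decision is part of the endpoint definition. A belief that one arm is winning could shift it, or could shift how symptoms are recorded.

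Retention is exposed too. Under Quality assurance, intervention can be stopped for insufficient adherence, with no threshold given, and data are collected only until participation ends.

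The article itself recognises how sensitive the endpoint is to the behaviour of staff and patients. Its Discussion warns that close monitoring may raise the number of exacerbations found in the intervention arm, and it concedes possible performance bias. The reason given for having no committee, minimal risk, answers a safety question and not this one. Once results have been circulated, no later analysis can remove their influence.

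**Working it through.** **1. The plan's own figure.** The stated sample size is 391. A median 30% shorter in controls gives, under exponential survival, a hazard ratio (HR) of 0.70. With two-sided α = 0.05 (sidedness is not stated) and power 0.80, Freedman's formula gives events = (1.960 + 0.842)² × (1.7/0.3)² ≈ 252.04, rounded up to 253. Take 25% event-free at 12 months in the intervention arm. The 12-month event probabilities are then 0.75 and 1 − 0.25^(1/0.7) = 0.862, mean 0.806. So N = 253/0.806 ≈ 314, and 314/0.8 ≈ 393. Schoenfeld variants give 384 or 394. The 391 is therefore consistent with a single-look design.

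**2. Inputs for the exposure calculation.**
- From the article: 402 patients, 1:1; recruitment March to end September 2021 (about 7 months); preparation up to six weeks and adherence assessment at least four; 18 months of intervention; 25% event-free at 12 months; 20% dropout.
- Assumed: uniform accrual; a lag L of 4 to 10 weeks (0.92 to 2.30 months) to intervention start; the 25% refers to controls; dropout is exponential over 18 months; the interim cutoff is calendar month 12.

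**3. Rates per month.**
- Control hazard: −ln(0.25)/12 = 0.1155
- Intervention hazard: 0.7 × 0.1155 = 0.0809
- Dropout: δ = −ln(0.8)/18 = 0.0124

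**4. Events by the end.** P(t) = λ/(λ+δ) × [1 − exp(−(λ+δ)t)]. At t = 18, P is 0.813 (control) and 0.705 (intervention). Total: 201 × (0.813 + 0.705) ≈ 305.

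**5. Events at the cutoff.** A patient enrolled at month a has t = 12 − a − L. P(t) is averaged over a from 0 to 7.

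| Lag | Mean P, control | Mean P, intervention | Events | Share of 305 | Still open |
|---|---|---|---|---|---|
| 4 weeks | 0.549 | 0.432 | 197 | 65% | 35% |
| 10 weeks | 0.481 | 0.372 | 171 | 56% | 44% |

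About 180 to 209 patients are then still followed without an event. Recruitment has closed by this date, so what is exposed is ascertainment and retention, not enrolment.

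**6. Allowing for circulation time.** If results reach staff three months after cutoff (an assumption), events are about 241 and 223, or 79% and 73%. That leaves 21-27% open.

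**7. Another reading of the date.** If the interim falls after 12 months of intervention for each patient, the fraction accrued (ignoring dropout, HR 0.7 to 1) is 0.84-0.86, leaving about 14-16% open.

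**8. Type I error, conditional only.** If the primary endpoint were tested at 5% at both looks, the bivariate normal with correlation √0.56 to √0.65 gives an overall two-sided error of 8.1% to 7.8%. With no efficacy decision at the interim, there is no inflation and 391 stands.

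**The case against.** The strongest reply is that the article never says the interim is comparative. It sits beside recruitment reports and device alerts, so it could be a progress or data-quality review. The recipients are undefined and might be consortium partners rather than every treating physician. Staff know allocations from the first day, so differing antibiotic thresholds are possible with or without an interim. Coaching frequency is fixed by adherence and calendar, so interim results would not readily change it.

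Much of this stands. By-arm content and physicians among the recipients are inferences, the first from the general between-arm analysis and the second from an unrestricted grant of access. The increment of bias from knowing the overall comparison cannot be computed. The 35-44% is an upper figure, since it allows no time between cutoff and circulation.

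A reader might also infer that the plan lacks alpha control and inflates type I error. The document does not support that. It states no interim test of the primary endpoint, no early stop and no early efficacy claim. Boundaries are commonly left to a full protocol or analysis plan, which is not shown here. The 7.8-8.1% belongs to a test that nobody has stated.

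What does not fall is the access rule. It is stated, not left out, and a fuller document could restrict access only by contradicting it.

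**Conclusion.** The point holds as an avoidable risk to trial integrity, not as a demonstrated bias. The plan opens interim results to all collaborators, with no independent committee and no stated restriction, in an unblinded trial with an antibiotic-dependent primary event. If the results are comparative and reach site physicians, then under the listed assumptions 35-44% of primary events are open at cutoff, or about 21-27% after a three-month delay. The shares depend on accrual pattern, lag, event rate and the reading of the interim date. Neither the size nor the direction of any resulting bias can be derived. No finding is made on alpha or type I error. This is a cheap improvement worth making before the interim takes place.

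**What to change.** Replace the access sentence under Quality assurance. Any by-arm interim results stay with the analysing institute until database lock. Sites, coaches, device and app partners, and investigators see only pooled recruitment, data completeness and total event counts. Add that the interim makes no between-arm efficacy test of the primary endpoint, which also settles the multiplicity question without changing the sample size.

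The cost is a short protocol amendment, with no extra patients and no change to clinical management. The one downside is that collaborators wait until the end of the trial for arm-level results. The amendment has to precede the interim.

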### Sample size calculation

Sample size calculation was performed by Private Institute for Applied Health Services Research (inav) GmbH and is based on the following assumptions: (1) primary endpoint: time to pulmonary exacerbation (30), (2) median time to exacerbation is 30% less in the CG compared to the IG based on estimation of involved CF experts, (3) event-free survival within 12 months in 25% of participants (18), (4) a significance level α = 0.05 and power of 1 – β = 0.8, (5) dropout rate of 20% (18) and (6) exponential distribution of survival and proportional hazards. Following these assumptions, a sample size of 391 participants is needed. To account for possible deviations from the assumed survival and dropout rate, we aim to recruit 402 patients. Participants are recruited as part of their routine visit at their CF centre by research personnel.

### Statistical analysis plan

All data will be analysed between IG and CG (cross-sectional analysis) as well as longitudinally. For the descriptive data analysis, adequate location and dispersion measures will be determined, and correlation analysis will be performed. An inferential data analysis will follow this. Depending on the kind of data and data distribution appropriate statistical tests will be applied: e.g. t-test, Wilcoxon-Rank-test, Friedman-tests or variance analysis with repetitive measures in order to identify longitudinal differences; e.g. log rank-test, WiIcoxon–Mann–Whitney-test and Chi-square-test for cross-sectional analysis. To investigate the relationships between the variables, multivariate analysis and regression analysis will be performed. An intention-to-treat-analysis will be used and further evaluated for its sensitivity according to per-protocol-principles and as-treated principles.

For the cost- effectiveness analysis the defined primary outcome parameter will be set against determined costs:$${\text{ICER}} = \frac{{{\text{Mean}}\;{\text{health}}\;{\text{costs}}\;{\text{in}}\; {\text{IG}} - {\text{Mean}}\;{\text{health}}\;{\text{costs}}\; {\text{in}}\;{\text{ CG}}}}{{{\text{Median}}\;{\text{time}}\;{\text{to}}\;{\text{exacerbation}}\;{\text{ in}}\;{\text{IG}} - {\text{Median}}\;{\text{time}}\;{\text{to }}\;{\text{exacerbation}}\;{\text{in}}\;{\text{CG}} }}$$

To account for uncertainty in estimation of ICER (incremental cost-effectiveness ratio), a non-parametric bootstrapping will be performed. Additionally, cost-effectiveness-acceptability-curves will be generated.

Qualitative data acquired from the telephone interviews will be transcribed verbatim and analysed via the data analysis program MAXQDA.

Using the EDC systems minimizes missing data. In the case missing or implausible data, study centres will be contacted and data possibly corrected. Alternatively, we will assess if appropriate imputation methods can be applied.

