### Randomization

A 1:1 randomization to the intervention group (IG) and control group (CG) is performed by an electronic-data-captures-system (EDC-Systems, secuTrial^®^) across the participating centres following study inclusion. Participants are stratified by age (12–17 years and ≥ 18 years of age), sex, CFTR modulator therapy, and lung function (FEV1 < 40% and FEV1 ≥ 40% predicted value at baseline/screening).

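### Randomisation is stratified on four factors, but the example tests neither use them nor adjust for baseline: a free improvement in precision

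*Protocol article*

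**What the plan says.** The Randomization section of the protocol article sets 1:1 allocation stratified by age (12–17 versus 18 and over), "sex, CFTR modulator therapy, and lung function" (FEV1 below 40% versus 40% predicted or more). That is four binary factors, or 16 cells.

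The Statistical analysis plan section leaves the choice of test to the type and distribution of the data and gives examples: "e.g. t-test, Wilcoxon-Rank-test, Friedman-tests or variance analysis with repetitive measures in order to identify longitudinal differences; e.g. log rank-test". Mann-Whitney and chi-square tests follow the log-rank test for the comparison of intervention group (IG) with control group (CG). The section then plans multivariate and regression analysis to study how variables relate to each other, without linking it to the treatment comparison or the stratification factors. It specifies intention-to-treat. For missing data it plans queries to the centres and, failing that, an assessment of whether imputation is suitable.

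The Endpoints section defines FEV1 and FVC as changes from baseline and quality of life as changes. The Sample size calculation section assumes a "dropout rate of 20" percent.

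**The concern.** A factor is normally chosen for stratification because it is expected to predict outcome. The article points the same way: its Background says CFTR-directed therapies reduce exacerbations and calls the extent of lung disease the most important prognostic factor for survival.

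Stratified allocation balances prognostic factors between the arms. An analysis that ignores them does not credit that balance, so its standard error is somewhat too large and power is given away. For a continuous outcome, an unadjusted test of change is less efficient than one that adjusts for the baseline value.

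There is a separate issue for repeated outcomes. Friedman tests and classical repeated-measures ANOVA need every visit from every participant analysed, and the Friedman test has no term for arm. Power on the primary endpoint, precision on the main secondary endpoints and use of partial follow-up are at stake. The validity of the trial is not.

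**Working it through.** **1. The plan's own sample size.** The inputs, all from Sample size calculation, are "a significance level α = 0.05 and power of 1 – β = 0.8" (two-sided assumed), "median time to exacerbation is 30% less in the CG compared to the IG", "event-free survival within 12 months in 25% of participants" (arm not stated), 20% dropout and "exponential distribution of survival and proportional hazards".

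- With exponential times, HR (IG/CG) = CG median / IG median = 0.70.
- Schoenfeld events: 4 × (1.960 + 0.842)² / (ln 0.70)² = 246.8, so 247.
- Freedman events: (1.70/0.30)² × (1.960 + 0.842)² = 252.04, so 253.
- If the 25% belongs to the IG, the CG is event-free in 0.25^(1/0.7) = 0.138. The mean event probability at 12 months is 1 − (0.25 + 0.138)/2 = 0.806.
- N = 253 / 0.806 / 0.80 = 392.4, so 393, against the stated 391.

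Other readings within 3% run from 384 to 396, and none gives exactly 391. Every matching formula is unstratified and unadjusted, so the stated size does not rely on adjustment.

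**2. Primary endpoint: Cox model with and without the four factors.** The simulation used N = 402, CG hazard −ln(0.25)/12 per month, conditional HR 0.70, 18 months of follow-up, 20% exponential dropout, stratified allocation and 3,000 runs. The documents give neither the prevalence nor the effect of the factors. Prevalences of 20/50/50/20% are assumed, and the effect is varied.

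| HR per factor | Power, unadjusted | Power, adjusted | Mean HR, unadjusted | Mean HR, adjusted | Type I error, unadjusted | Type I error, adjusted |
|---|---|---|---|---|---|---|
| 1.0 | 87.4% | 87.6% | 0.70 | 0.70 | 0.053 | 0.055 |
| 1.25 | 86.5% | 88.1% | 0.71 | 0.70 | 0.039 | 0.046 |
| 1.5 | 82.5% | 86.9% | 0.72 | 0.70 | 0.038 | 0.051 |
| 2.0 | 76.1% | 86.7% | 0.74 | 0.70 | 0.024 | 0.044 |

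The gains are 0.2, 1.6, 4.4 and 10.6 points. Monte Carlo error is about √(0.87 × 0.13 / 3,000) = 0.6 points for power and √(0.05 × 0.95 / 3,000) = 0.4 points for type I error. Power starts above 80% because, with 25% event-free in the CG at 12 months and 18 months of follow-up, about 338 participants would suffice.

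**3. The alternative of stratifying the log-rank test over all 16 cells.** Under the same assumptions with 4,000 runs, power unstratified versus stratified is 87.4% v 85.4% (HR 1.0 per factor), 86.8% v 85.8% (1.25), 82.8% v 84.6% (1.5) and 73.7% v 83.8% (2.0). Sparse cells cost 1 to 2 points when the factors are null or weak. The Cox model with four covariates avoids that cost.

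**4. Continuous outcomes.** Let r be the correlation between baseline and follow-up (assumed, with equal variances). The variance of ANCOVA relative to an unadjusted change score is (1 − r²) / [2(1 − r)] = (1 + r)/2. Where ANCOVA has 80% power, the t-test on change has Φ(2.802 × √((1 + r)/2) − 1.960).

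| r | Variance ratio | Power, change score |
|---|---|---|
| 0.5 | 0.75 | 68% |
| 0.7 | 0.85 | 73% |
| 0.8 | 0.90 | 76% |
| 0.9 | 0.95 | 78% |

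Baseline adjustment therefore gains 2 to 12 points.

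**5. Partial series.** If the assumed 20% dropout interrupts the visit series, 0.20 × 402 = 80.4, so about 80 participants would have an incomplete row. A complete-row method could use them only after imputation.

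**The case against.** The strongest reply is that this is a condensed article. Its tests are examples, regression is planned, and covariate choice is ordinary content for an analysis plan that is not shown. That stands: nothing here excludes adjustment, and the article is not in error. What remains is that every example disregards the stratified design, while naming a better analysis costs nothing.

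Four stronger readings are tempting, and the documents do not support them.

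- **Incomplete cases will be dropped.** No complete-case rule is stated. Intention-to-treat is specified, imputation is to be considered, and the log-rank test censors incomplete follow-up. The figure of about 80 applies only to complete-row methods without imputation.
- **Baseline is ignored.** FEV1 and FVC are already changes from baseline. The gap is the lack of covariate adjustment.
- **The unadjusted hazard ratio is biased.** The shift from 0.70 towards 0.74 in the table is non-collapsibility: marginal and conditional hazard ratios are different quantities. The sample size section states its effect as a difference in medians between arms, which reads as marginal, whereas the simulation sets 0.70 as conditional. The unadjusted power of 76.1% is therefore not a shortfall against the plan's own assumption. The useful figure is the gap between the two analyses.
- **Power will be lost on the primary endpoint.** This depends on prognostic strength, which the documents do not give. A gain of about 10 points needs all four factors, sex included, to carry a hazard ratio of 2.

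**Conclusion.** The point holds as a free improvement. The example tests do not use the four stratification factors or adjust for baseline, and the planned regression is not attached to the treatment comparison.

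For the primary endpoint, the unadjusted test remains valid and errs on the conservative side when the factors are prognostic (simulated type I error down to 0.024). Adjustment by a Cox model gains from about nil to about 10 points of power, with no material loss in any scenario tried. For continuous outcomes the gain is 2 to 12 points over change scores, for assumed correlations of 0.9 down to 0.5. Friedman tests and classical repeated-measures ANOVA cannot use partial series unless imputation is applied.

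The sizes rest on assumed prevalences, factor effects and correlations. The direction does not depend on their exact values. A reader should not infer that the planned analysis is invalid, that the trial is underpowered, or that results will rest on completers.

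**What to change.** State the following in the analysis section, or confirm it in the full analysis plan.

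- **Primary endpoint:** a Cox model for time to first exacerbation, reporting the hazard ratio with its 95% confidence interval, adjusted for age group, sex, CFTR modulator therapy and FEV1 class. Keep the unadjusted log-rank test as a sensitivity analysis.
- **FEV1, FVC, CFQ-R and EQ-5D:** compare the arms with a mixed model for repeated measures on all available visits, with arm by visit, the baseline value and the four stratification factors.

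Entering FEV1 as a continuous value and adding centre are optional. Centre is not among the listed stratification factors, and neither option was simulated here.

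The cost is wording only. The stratification factors are known at randomisation, and Table 1 schedules lung function and both quality-of-life questionnaires at inclusion and at the start of the intervention. No new data are needed, and the sample size need not change. The choice should be fixed before any outcome comparison is seen, because the trial is unblinded and the Quality assurance section gives all collaborators access to the interim results.

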Lung function test	IG/CG		IG/CG	IG/CG	IG/CG	IG/CG
Therapy plan	IG/CG		IG/CG	IG/CG	IG/CG	IG/CG
Pulmonary exacerbations since last study visit	IG/CG		IG/CG	IG/CG	IG/CG	IG/CG
Time period until first pulmonary exacerbation since beginning of study intervention				IG/CG	IG/CG	IG/CG
Time between pulmonary exacerbations since last study visit	IG/CG		IG/CG	IG/CG	IG/CG	IG/CG
CF-associated hospital admissions since last study visit	IG/CG		IG/CG	IG/CG	IG/CG	IG/CG
Days absent from work or school since last study visit				IG/CG	IG/CG	IG/CG
CF-associated medical treatment and care since last study visit				IG/CG	IG/CG	IG/CG
Telemonitoring (App)						
Continuous monitoring of adherence to inhalation therapy		IG/CG	IG/CG	IG/CG	IG/CG	IG/CG
		continuously				
Weekly lung function measured by home spirometry^a^			IC	IC	IC	IC
			at least 1x/week			
Patient questionnaire						
Quality of life: EQ-5D-5L /. EQ-5D-Y-5L	IG/CG		IG/CG	IG/CG	IG/CG	IG/CG
Quality of life: CFQ-R	IG/CG		IG/CG	IG/CG	IG/CG	IG/CG
Beck Depression Inventar	IG/CG		IG/CG	IG/CG	IG/CG	IG/CG
Expectations and their fulfilment regarding the new form of care	IG/ relatives					IG/ relatives
Telephone interview						
acceptance, satisfaction, potential for optimization, barriers and implementation into standard care						IG/physician/ relatives

IG = intervention group, CG = control group, t_0_ = inclusion into study, t_1_ = start assessment of adherence, t_2_ = start study intervention, t_3_ = six months of study intervention, t_4_ = 12 months of study intervention, t_5_ = end of study intervention

^a^Lung function is measured at least weekly by home spirometry

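### The ICER divides a difference in mean costs by a difference in median time to first exacerbation, so it is not a cost per exacerbation-free month gained

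*Protocol article*

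**What the plan says.** The section Statistical analysis plan of the protocol article introduces the cost-effectiveness analysis with the words "the defined primary outcome parameter will be set against determined costs" and then prints a formula. The numerator is mean health costs in the intervention group (IG) minus mean health costs in the control group (CG). The denominator is median time to exacerbation in the IG minus the same median in the CG. No other effect measure is named for this analysis, and the formula gives no cost horizon.

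For uncertainty, "a non-parametric bootstrapping will be performed", and "cost-effectiveness-acceptability-curves will be generated".

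The effect parameter is set out under Endpoints: "The primary endpoint is the time to first protocol-defined pulmonary exacerbation after initiation of the intervention phase". The same section adds that "health care-related costs for both study groups are evaluated". The abstract places costs among the exploratory assessments. Table 1 records CF-related treatment and care at t3, t4 and t5 of the 18-month intervention phase, and lists "Quality of life: EQ-5D-5L /. EQ-5D-Y-5L" for both arms at t0 and t2 to t5.

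**The concern.** A payer's total cost is the number of patients times the mean cost, and the total benefit is the number of patients times the mean benefit. That is why a cost-effectiveness ratio is built from means. A difference in medians compares the two survival curves only at the 50% level and does not scale up in this way. Dividing mean cost by it gives a number in euros per month that is not the cost of one additional exacerbation-free month per patient. An acceptability curve built on it has a willingness-to-pay axis without that meaning.

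This is a formula the article commits to, not a detail left to a fuller document. It matters because the Discussion presents cost-effectiveness as one of the grounds on which new forms of care are to be judged and as part of the case for routine use.

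**Working it through.** **Inputs** (section Sample size calculation unless noted)
- Exponential survival with proportional hazards. The CG median is 30% below the IG median, so the hazard ratio (HR) is 0.70.
- 25% event-free at 12 months. The arm is not stated, so both readings are carried: the figure belongs to the CG, or to the IG.
- Alpha 0.05 (two-sided assumed), power 0.80, dropout 20%, stated N 391, target 402 (201 per arm).
- Intervention phase of 18 months (Study flow and study intervention). Taking costs over this phase is an inference.

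**Step 1. Check the inputs against the plan's own N.** Freedman's formula at HR 0.70 gives 253 events. With 25% event-free in the IG, the 12-month event probabilities are 0.75 (IG) and 0.862 (CG), mean 0.806. Then 253 / 0.806 / 0.8 = 392.4, so 393 against the stated 391. With 25% in the CG and events counted over 18 months, the mean event probability is 0.821 and N is 253 / 0.821 / 0.8, about 386. Both are close to 391, so N does not settle which arm was meant.

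**Step 2. Hazards.** A 25% event-free share at 12 months gives λ = ln 4 / 12 = 0.1155 per month.
- CG reading: CG 0.1155; IG 0.1155 × 0.7 = 0.0809.
- IG reading: IG 0.1155; CG 0.1155 / 0.7 = 0.1650.

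**Step 3. Three effect measures.** Median = ln 2 / λ; full mean = 1 / λ; restricted mean to 18 months = (1 − exp(−18λ)) / λ. Values in months:

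| Measure | CG reading: IG − CG | IG reading: IG − CG |
|---|---|---|
| Median | 8.57 − 6.00 = 2.57 | 6.00 − 4.20 = 1.80 |
| Restricted mean, 18 months | 9.48 − 7.57 = 1.91 | 7.57 − 5.75 = 1.83 |
| Full mean | 12.37 − 8.66 = 3.71 | 8.66 − 6.06 = 2.60 |

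**Step 4. Effect on the ICER.** For a given cost difference, the printed ICER divided by a mean-based ICER equals the mean difference divided by the median difference.
- Against the restricted mean: 1.91 / 2.57 = 0.74 (CG reading); 1.83 / 1.80 = 1.01 (IG reading).
- Against the full mean: 1 / ln 2 = 1.44 in both readings.

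For a purely illustrative cost difference of 1,000 EUR, the ICER per month (CG / IG reading) is 389 / 556 from medians, 524 / 548 from restricted means and 270 / 385 from full means.

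**Step 5. Sampling noise of the denominator.** 4,000 trials were simulated with 201 per arm, 20% exponential dropout over 18 months, and Kaplan-Meier estimates of the median and restricted mean.

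| Scenario | Measure | Coefficient of variation | Share ≤ 0 |
|---|---|---|---|
| HR 0.70, CG reading | Median | 1.09 / 2.55 = 0.43 | 0.7% |
| | Restricted mean | 0.64 / 1.89 = 0.34 | 0.2% |
| HR 0.70, IG reading | Median | 0.76 / 1.81 = 0.42 | 0.6% |
| | Restricted mean | 0.56 / 1.83 = 0.31 | 0.1% |
| HR 0.85 (assumed), CG reading | Median | 0.98 / 1.03 = 0.95 | 14% |
| | Restricted mean | 0.62 / 0.86 = 0.73 | 8% |

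The median could be estimated in both arms of every simulated trial.

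**The case against.** The strongest reply is that the size of the error is not fixed. If the 25% belongs to the IG, the printed ratio and the 18-month restricted-mean ratio differ by about 1%. That stands. A reader might infer that the printed ICER is simply 26% too low, but this needs both the CG reading, which the article does not state, and the restricted mean as comparator. Against the full mean the printed ICER is 44% too high. The near-agreement in the IG reading comes from these particular hazards and this horizon; it does not turn a median into a mean effect.

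A reader might also infer that the ratio is unusable because the median will often not be reached or the denominator will change sign. The plan's own figures do not support this. The medians lie between 4.2 and 8.6 months in an 18-month phase, and a denominator at or below zero is rare at HR 0.70. The Discussion warns that closer monitoring could raise the number of exacerbations in the IG. If that shortened the time to the first one, the restricted-mean difference would turn negative as well. Fragility near a zero effect belongs to any ICER.

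It is also true that costs may continue to accrue after the first exacerbation while the effect stops there. Restricted mean time to first exacerbation shares that limit, so it is not an argument against the median alone.

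Finally, bootstrapping and acceptability curves are already planned, and nothing in the article says that costs and effects would be resampled separately. The economic analysis is exploratory. These points lower the severity but leave the mismatch between mean and median in place.

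**Conclusion.** The concern holds as a mismatch of estimands: mean cost over median effect does not estimate incremental cost per exacerbation-free month gained per patient. This follows from the printed formula and needs no numerical assumption.

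The size does rest on assumptions: exponential survival, HR 0.70, an 18-month horizon inferred for costs, and an unstated arm for the 25% figure. On these the printed ICER ranges from 26% below to 1% above the restricted-mean ICER, and is 44% above the full-mean ICER, so no single direction of bias can be claimed. The loss of precision is real but moderate at the design effect.

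This should be fixed before the economic data are analysed. It does not touch the primary test or the sample size, and the trial's efficacy conclusion is not in question.

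**What to change.** 1. Replace the denominator by the difference in restricted mean exacerbation-free time over the same horizon as the costs, and state that horizon (18 months if costs are taken over the intervention phase). The full mean is a poorer choice because it needs extrapolation: on the plan's assumptions 5% to 23% of an arm are still event-free at 18 months.
2. State that the bootstrap resamples each patient's cost and effect together.
3. Derive the acceptability curve from incremental net benefit, so that small or negative effects stay interpretable.
4. Optionally, because restricted mean time also stops at the first exacerbation, add a mean effect that covers the whole cost horizon: mean exacerbations avoided, or QALYs from the EQ-5D data already collected.

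The cost is a changed formula, a sentence on the horizon and a small amount of extra analysis. No new data are needed.
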